| To evaluate the safety and tolerability of multiple doses of CM313 in subjects with systemic lupus erythematosus (SLE).                                                                                                                                                                                     | Safety endpoints: adverse events (AEs), laboratory tests, physical examinations, vital signs, 12-lead electrocardiogram (ECG) abnormalities, etc.                                                                                                                                                                                                                                                                                                                                                                                                                                                                                                                                                                                                                                                                                                                                                                                                                                                                                                                                                                                                                                                                                          |

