14. Blood chemistry: including glucose, total cholesterol, low density lipoprotein cholesterol, high density lipoprotein cholesterol, alanine aminotransferase, aspartate aminotransferase, total protein, albumin, total bilirubin, direct bilirubin, lactate dehydrogenase, alkaline phosphatase, glutamyl transpeptidase, creatinine, urea/urea nitrogen, uric acid, sodium, potassium, chloride, calcium. Serum chemistry results within 3 days prior to the first dose will be acceptable at the baseline visit.

15. Coagulation: including prothrombin time, activated partial thromboplastin time, thrombin time, fibrinogen and international normalized ratio. Coagulation results within 3 days prior to the first dose will be acceptable at the baseline visit.
16. Urinalysis: including urine protein, glucose, ketones, occult blood, microscopic examination (including red blood cells/high power field, white blood cells/high power field, poikilocytes, casts and specific classification), urobilinogen, urine bilirubin, nitrite, urine specific gravity, and acidity or alkalinity. Urinalysis results within 3 days prior to the first dose will be acceptable at the baseline visit. If the subject is menstruating, the urinalysis may be postponed until after the menstrual period.
17. Pregnancy test: for women of childbearing potential only. Blood pregnancy tests will be performed at the screening visit and the EOS visit, while blood or urine pregnancy tests will be performed at other visits. Unscheduled blood or urine pregnancy tests may be performed at the investigator's discretion during the course of the study.
18. 24-hour urine protein will only be conducted for subjects whose urine protein/creatinine ratio exceeds the ULN during the screening period. The 24-hour urine protein and urine protein/creatinine ratio at the baseline visit can be completed on D1 or within 48 hours before D1. The 24-hour urine protein and urine protein/creatinine ratio within 3 days prior to the first dose are acceptable at the baseline visit.
19. Immunology-related endpoints: including IgG, IgA, IgM, IgE, complement (C3, C4), and anti-ds-DNA antibody. These will be tested by the laboratories of each study site during the screening period. Baseline and subsequent examinations will be conducted by the central laboratory. Among them, the results of IgG, IgA, IgM, and IgE at baseline and thereafter will not be provided to each study site before unblinding to avoid breaking of blindness.

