In terms of safety, no DLTs have been observed to date. Treatment-emergent adverse events (TEAEs) occurred in 9/10 subjects, and treatment-related adverse reactions (TRAEs, i.e., IMP-related AEs) occurred in 7/10 subjects. However, the vast majority of TEAEs and all TRAEs were grade 1 or 2. The most common (incidence  $\geq 2/10$ ) TEAEs were infusion-related reactions (IRRs) (5/10), upper respiratory tract infection (3/10), hypokalemia (2/10), hyponatremia (2/10), hypertriglyceridemia (2/10), and back pain (2/10). The TRAEs experienced by the subjects were: IRR (5/10), aspartate aminotransferase (AST) increased (1/10), lymphopenia (1/10), hypertriglyceridemia (1/10), peripheral neuropathy (1/10), and rash (1/10). A total of 9 grade 3 TEAEs (no grade 4 or higher TEAEs) occurred in 4/10 subjects, all of which were unrelated to CM313 treatment.

In terms of efficacy, in the accelerated dose escalation low-dose levels (0.06, 0.3, and 1 mg/kg), all 3 subjects discontinued treatment due to disease progression. Additionally, 1 subject in the lowest dose level (0.006 mg/kg) withdrew voluntarily, with a neoplasm assessment finding of stable disease (SD). The best efficacy assessment findings for the 3 subjects in the 2 mg/kg dose level were very good partial response (VGPR), minor response (MR), and SD, respectively. For the 2 subjects in the 4 mg/kg dose level who had completed the first efficacy assessment, the neoplasm assessment findings were SD and VGPR, respectively. Currently, only 6 subjects in the 2 mg/kg and 4 mg/kg dose levels remain on CM313 study treatment.

Regarding PK, as shown in the table below, the mean PK parameters in 3 subjects in the 2 mg/kg dose level and 2 subjects in the 4 mg/kg dose level were similar to the mean PK parameters of daratumumab at the same dose. The clearance rate showed a decreasing trend with increasing dose and number of administrations, while the half-life showed an increasing trend with increasing dose and number of administrations, both exhibiting non-linear PK characteristics, suggesting target-mediated clearance of CM313.

| Parameter | CM313 dose level |
|-----------|------------------|
|-----------|------------------|

|                                        | 2 mg/kg             | 4 mg/kg           |
|----------------------------------------|---------------------|-------------------|
| Cmax (µg/mL)         |                     |                   |

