| Hematology           | Red blood cells, hemoglobin, white blood cells, hematocrit, platelets, neutrophil count and percentage, lymphocyte count and percentage, monocyte count and percentage                                                                                                                                                                                                        |
| Blood Chemistry      | Glucose, total cholesterol, low density lipoprotein cholesterol, high density lipoprotein cholesterol, alanine aminotransferase, aspartate aminotransferase, total protein, albumin, total bilirubin, direct bilirubin, lactate dehydrogenase, alkaline phosphatase, glutamyl transpeptidase, creatinine, urea/urea nitrogen, uric acid, sodium, potassium, chloride, calcium |
| Urinalysis           | Urine protein, urine glucose, ketones, occult blood, microscopic examination (including red blood cells/HPF, white blood cells/HPF, poikilocytes, casts and                                                                                                                                                                                                                   |

|             |                                                                                                                    |
|-------------|--------------------------------------------------------------------------------------------------------------------|
|             | specific classification), urobilinogen, urine bilirubin, nitrite, urine specific gravity, acidity or alkalinity.   |
| Coagulation | Prothrombin time, activated partial thromboplastin time, thrombin time, fibrinogen, international normalized ratio |

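### The scheduled blood chemistry panel measures three cholesterol fractions but not triglycerides, although the earlier CM313 study reported hypertriglyceridemia

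*Protocol*

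**What the plan says.** The Synopsis makes laboratory results part of the primary endpoint: "Safety endpoints: adverse events (AEs), laboratory tests, physical examinations, vital signs, 12-lead electrocardiogram (ECG) abnormalities, etc". The chemistry content is fixed in two places. Table 1, note 14, begins "Blood chemistry: including glucose, total cholesterol, low density lipoprotein cholesterol, high density lipoprotein cholesterol, alanine aminotransferase, aspartate aminotransferase", and the Section 3.9.1 table begins "Glucose, total cholesterol, low density lipoprotein cholesterol, high density lipoprotein cholesterol, alanine aminotransferase, aspartate aminotransferase, total protein, albumin". Both continue to the same 20 analytes. Section 5.2.4 points to Section 3.9.1 for the content of the laboratory tests and schedules them at all 14 visits, V1 to V14. Section 8.3.8.3 analyses them with shift tables of baseline against post-baseline results.

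Section 1.3.2 describes the only earlier clinical study of the drug, in 10 myeloma patients. The common treatment-emergent events there included "hypokalemia (2/10), hyponatremia (2/10), hypertriglyceridemia (2/10), and back pain (2/10"). The events judged related to the drug included "lymphopenia (1/10), hypertriglyceridemia (1/10), peripheral neuropathy (1/10), and rash (1/10"). On severity, "the vast majority of TEAEs and all TRAEs were grade 1 or 2".

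**The concern.** The panel already covers lipids, so lipid safety was not left out on purpose, and no reason is given for stopping at cholesterol. The missing lipid is the one that the protocol's own background reports as an event with CM313. This trial's main purpose is safety in a new population, and it plans 8 and 16 mg/kg, above the 4 mg/kg reached in the earlier data cited. If triglycerides are not scheduled, the final laboratory tables will be silent on them whatever the drug does, and a reader could take that silence for reassurance. An analysis plan cannot repair this, because it cannot create results that were never collected. Section 8.3.12 also says that missing safety data will not be handled.

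**Working it through.** There is no figure in the plan to reproduce: Section 8.1 states that the sample size rests on no statistical calculation. The point rests on setting the sections side by side. The arithmetic below only shows how weak or strong the earlier signal is.

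**1. Panel content.** Counting the entries in note 14 gives 20. The lipids are total, LDL and HDL cholesterol. Triglycerides appear 0 times. Section 3.9.1 agrees, and no other section schedules the test.

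**2. Earlier laboratory-type events against this trial's panels.**

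| Event in Section 1.3.2 | Reported as | Analyte scheduled here |
|---|---|---|
| Hypokalemia | TEAE 2/10 | Potassium: yes |
| Hyponatremia | TEAE 2/10 | Sodium: yes |
| AST increase | Related 1/10 | AST: yes |
| Lymphopenia | Related 1/10 | Lymphocyte count: yes |
| Hypertriglyceridemia | TEAE 2/10, related 1/10 | Triglycerides: no |

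Four of the five are covered.

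**3. How a rise could still reach the data.** The shift tables need a baseline and later values, and neither is planned. Section 5.2.4 lets the investigator test more often but does not mention further analytes. What remains is a test done on a site's own initiative, recorded as an adverse event if judged clinically significant (Sections 4.4 and 6.3.1). That route is unsystematic and has no planned baseline.

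**4. Strength of the earlier signal.** Exact (Clopper-Pearson) 95% limits for x of n are the 2.5% quantile of Beta(x, n−x+1) and the 97.5% quantile of Beta(x+1, n−x).
- Related, 1/10: 0.3% to 44.5%.
- Any cause, 2/10: 2.5% to 55.6%.

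Assume, for illustration only, that a myeloma rate p carries over to lupus. The chance of at least one case among the 8 CM313 subjects of one dose level is 1 − (1 − p)^8:
- p = 5% (assumed): 1 − 0.95^8 = 34%.
- p = 10%: 1 − 0.90^8 = 57%.
- p = 20%: 1 − 0.80^8 = 83%.
- p at the limits for 1/10 (0.25% and 44.5%): 2% and 99%.

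The last line shows that the data hardly constrain the expected number of cases. Without the analyte, the scheduled tables hold no triglyceride data at any of these rates.

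**5. What the placebo group could add.** There are 2 placebo subjects per level, so 4 × 2 = 8 in all, or 3 × 2 = 6 if 16 mg/kg is not opened. Take a hypothetical 3 cases among 32 on CM313 and none among 8 on placebo. The one-sided Fisher p is C(32,3)/C(40,3) = 4,960/9,880 = 0.50. With 6 against none it is C(32,6)/C(40,6) = 906,192/3,838,380 = 0.24. The comparison can only be descriptive.

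**The case against.** The strongest reply is that nothing in the protocol is contradicted. Note 14 presents its list as inclusive and does not forbid other tests. The adverse event definition in Section 6.1.1 covers laboratory abnormalities in general, and Section 6.3.1 is not confined to the panel. Section 3.4 states that CM313 has no confirmed important risk, and hypertriglyceridemia is not among the potential ones it lists, so no monitoring commitment is broken. The signal is one low-grade event attributed to the drug among 10 relapsed or refractory myeloma patients, with no comparator described. Values would also be hard to read: neither note 14 nor Section 5.2.4 asks for fasting or times the draw against premedication, steroid is recommended around every infusion (Section 3.8.2.3), and Section 1.1 names hyperlipidemia as a glucocorticoid reaction.

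All of this stands, and it limits the point in three ways. A reader might infer that the primary endpoint cannot show this event at all. It can, through adverse events found by unscheduled testing; only the scheduled laboratory data are empty. A reader might infer that a harm of the drug is already known. One grade 1 or 2 related event does not establish that. A reader might infer that the placebo arm would separate a drug effect from a steroid effect. With 8 or 6 subjects and descriptive tables, it could not do so reliably.

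The objection does not give a reason for leaving the analyte out. A small, uncertain signal is what a safety study in a new population is meant to follow up, and systematic measurement is what replaces chance detection.

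**Conclusion.** The point holds as a gap in systematic measurement. Both definitions of the panel omit triglycerides, so the laboratory part of the primary safety endpoint has neither a planned baseline nor a shift table for them. This is the only one of the five laboratory-type events listed in Section 1.3.2 that the scheduled panels do not cover. How many subjects might be affected cannot usefully be estimated: the interval for the related rate is 0.3% to 45%, and any projection assumes that a rate from myeloma patients applies in lupus. The finding supports an inexpensive improvement to monitoring. It does not show that the rest of the safety assessment is compromised.

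**What to change.** Add triglycerides to the blood chemistry list in both Table 1 note 14 and Section 3.9.1, run on the samples already drawn at baseline and each chemistry visit. Include them in the Section 8.3.8.3 shift tables. Record with each sample whether the subject was fasting and when it was drawn relative to steroid premedication. If the sponsor prefers to leave triglycerides out, the protocol should say why.

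The cost is one analyte on existing samples, a line in the laboratory manual and a few eCRF fields, with no added visit. The small downside is that non-fasting or post-steroid values need cautious reading. The recorded fields make such values identifiable but do not remove the confounding.

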**Table 2 Pharmacokinetic, Pharmacodynamic, and Immunogenicity Blood Sampling Schedule**

|                                     | PK blood sample collection                                                                                                                                                                                                                                                                                                                                                                           | PD blood sample collection
(immune cell typing)                                                                                                                                         | PD blood sample
collection (IFN-I related
gene expression)                                                         | Immunogenicity
blood sample
collection                                                                             |
|-------------------------------------|-------------------------------------------------------------------------------------------------------------------------------------------------------------------------------------------------------------------------------------------------------------------------------------------------------------------------------------------------------------------------------------------------------------|----------------------------------------------------------------------------------------------------------------------------------------------------------------------------------------------------|-----------------------------------------------------------------------------------------------------------------------------------|-----------------------------------------------------------------------------------------------------------------------------------|
| First dose                   | Within 2 hours before the start of infusion, 3 hours ( $\pm 15$ min) after the start of infusion, at the end of infusion (within 5 min), and at 2 hours ( $\pm 15$ min), 5 hours ( $\pm 30$ min), 24 hours ( $\pm 2$ h), 72 hours ( $\pm 4$ h), 168 hours ( $\pm 24$ h), 336 hours ( $\pm 24$ h), 504 hours ( $\pm 72$ h) after the end of infusion                                                         | Within 2 hours before the start of infusion, and at 24 hours ( $\pm 2$ hours), 168 hours ( $\pm 24$ hours), 336 hours ( $\pm 24$ hours), and 504 hours ( $\pm 72$ hours) after the end of infusion | Within 2 hours before the start of infusion and at 168 hours ( $\pm 24$ hours) after the end of infusion                          | Within 2 hours before the start of infusion                                                                                       |
| Second dose                  | Within 2 hours before the start of infusion                                                                                                                                                                                                                                                                                                                                                                 | Within 2 hours before the start of infusion and at 24 hours ( $\pm 2$ hours) after the end of infusion                                                                                             | Within 2 hours before the start of infusion                                                                                       | Within 2 hours before the start of infusion                                                                                       |
| Third dose                   | Within 2 hours before the start of infusion                                                                                                                                                                                                                                                                                                                                                                 | NA                                                                                                                                                                                                 | NA                                                                                                                                | NA                                                                                                                                |
| Fourth dose                  | Within 2 hours before the start of infusion                                                                                                                                                                                                                                                                                                                                                                 | NA                                                                                                                                                                                                 | NA                                                                                                                                | NA                                                                                                                                |
| Last dose                    | Within 2 hours before the start of infusion, 3 hours ( $\pm 15$ min) after the start of infusion, at the end of infusion (within 5 min), and at 2 hours ( $\pm 15$ min), 5 hours ( $\pm 30$ min), 24 hours ( $\pm 2$ h), 72 hours ( $\pm 4$ h), 168 hours ( $\pm 24$ h), 504 hours ( $\pm 72$ h), 840 hours ( $\pm 72$ h), 1176 hours ( $\pm 72$ h), and 1512 hours ( $\pm 72$ h) after the end of infusion | Within 2 hours before the start of infusion, and at 24 hours ( $\pm 2$ h), 840 hours ( $\pm 72$ h), and 1512 hours ( $\pm 72$ h) after the end of infusion                                         | Within 2 hours before the start of infusion and at 840 hours ( $\pm 72$ h) and 1512 hours ( $\pm 72$ h) after the end of infusion | Within 2 hours before the start of infusion and at 840 hours ( $\pm 72$ h) and 1512 hours ( $\pm 72$ h) after the end of infusion |
| At early withdrawal (if applicable) |                                                                                                                                                                                                                                                                                                                                                                                                             |                                                                                                                                                                                                    |                                                                                                                                   |                                                                                                                                   |

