| 
 
➤ To evaluate the PK characteristics of multiple doses of CM313;
 
➤ To evaluate the PD characteristics of multiple doses of CM313;
 
➤ To evaluate the immunogenicity of multiple doses of CM313.
 
 | 
 
➤ PK endpoints: 
 
• PK parameters after the first dose of CM313, including time to maximum concentration (<math>T_{max}</math>), maximum concentration (<math>C_{max}</math>), area under the serum concentration-time curve over a dosing interval (<math>AUC_{tau}</math>), area under the serum concentration-time curve from time 0 to time t (<math>AUC_{0-t}</math>), etc.;
 
• PK parameters after the last dose of CM313, including <math>T_{max}</math>, <math>C_{max}</math>, <math>AUC_{tau}</math>, <math>AUC_{0-t}</math>, area under the concentration-time curve from 0 to <math>\infty</math> (<math>AUC_{0-\infty}</math>), elimination half-life (<math>T_{1/2z}</math>), clearance (CL), volume of distribution (<math>V_z</math>), mean residence time (<math>MRT_{0-t}</math>), and accumulation index (<math>R_{ac}</math>), etc.
 
 
 
➤ PD endpoints: 
 
• Changes and rates of change from baseline in immune cell subtypes, including T lymphocytes, B lymphocytes, pDC cells, and NK cells.
 
 
 
➤ Immunogenicity endpoints: Anti-drug antibodies (ADAs).
 
                                                                                    |

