### 3.8.2.3 Pre- and Post-infusion Medications of Investigational Medicinal Product Infusion Solution

To reduce the risk of IRRs, the following medications are recommended for each subject, before and after each IMP infusion:

Pre-infusion medications (within 1-3 hours before infusion):

- Corticosteroids (intermediate-acting or long-acting): It is recommended to administer 100 mg methylprednisolone (or equivalent drug) intravenously before the 1st and 2nd IMP administrations; starting from the 3rd IMP administration, the corticosteroid dose can be reduced to 60 mg methylprednisolone (or equivalent drug), orally or intravenously. If patients receive the aforementioned methylprednisolone (or equivalent drug) as pre-infusion medication on the IMP administration day, they should not receive additional corticosteroids as part of their standard SLE treatment.
- Paracetamol, 650 mg to 1000 mg, oral.
- Antihistamines: Diphenhydramine, 25 mg to 50 mg (or equivalent), oral or intramuscular.

Post-infusion medications:

- Starting from the day after the completion of the infusion, subjects should receive corticosteroids for 2 consecutive days (20 mg methylprednisolone or equivalent drug daily). If the oral corticosteroid dose in the subject's standard SLE treatment is  $\geq$  the above dose, no additional corticosteroids will be given; if the oral corticosteroid dose in the subject's standard SLE treatment is  $<$  the above dose, corticosteroids will be supplemented to the above dose).
- In addition, for subjects with a history of chronic obstructive pulmonary disease (COPD), post-infusion medications may be considered, including short-acting and long-acting bronchodilators and inhaled corticosteroids.

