### **3.8.8. Concomitant Therapies**

All drug therapy (including nutritional supplements) and non-drug therapy received by the subject from the time of signing the ICF until the last visit need to be collected and recorded in the electronic data capture (EDC) system.

To prevent IRRs, all subjects need to receive prophylactic medications before and after each infusion.

Subjects enrolled in this study need to maintain a stable standard of care regimen for at least 30 days before the first dose of IMP. After the subject is randomized and receives the first dose of IMP, the investigator can adjust the standard of care according to the changes in the subject's condition.

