### **5.5.2. Biomarker Sample Processing**

For immune cell phenotyping analysis, 3 mL of venous blood will be collected each time. For type I IFN-related gene expression, 3 mL of venous blood will be collected each time. All blood samples need to be sent to the central laboratory for testing after collection.

A separate Sample Management Manual will specify the sampling, storage, and transportation procedures to be followed for this study, and the sponsor will provide a Sample Management Manual prior to the start of the study.

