### **8.3.6. Pharmacodynamic Evaluation**

Descriptive statistics will be performed on the PD endpoints at each evaluation time point after treatment in each group, as well as their changes and percentage changes from baseline.

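### The only baseline for the immune-cell endpoint may be drawn before or after the 100 mg methylprednisolone premedication, and the protocol does not fix the order

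*Protocol*

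**What the plan says.** Table 2 times the first-dose immune-cell samples as "Within 2 hours before the start of infusion, and at 24 hours", then 168, 336 and 504 h after the end of infusion. The first-dose interferon-gene sample has the same 2-hour pre-dose window and one follow-up at 168 h. Table 2 lists no earlier pharmacodynamic (PD) sample, at screening or otherwise, so the pre-dose sample is the only possible baseline.

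The synopsis and Section 3.8.2.3 use the same premedication window: "Pre-infusion medications (within 1-3 hours before infusion". For the steroid, Section 3.8.2.3 states: "It is recommended to administer 100 mg methylprednisolone (or equivalent drug) intravenously before the 1st and 2nd IMP administrations". After infusion, "subjects should receive corticosteroids for 2 consecutive days (20 mg methylprednisolone or equivalent drug daily" applies, starting the next day.

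Section 3.8.2.3 words the premedication as a recommendation. Section 3.8.8 is firmer: "To prevent IRRs, all subjects need to receive prophylactic medications before and after each infusion".

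The secondary PD endpoint in Section 2 is "Changes and rates of change from baseline in immune cell subtypes, including T lymphocytes, B lymphocytes, pDC cells, and NK cells". Section 8.3.6 gives its analysis: "Descriptive statistics will be performed on the PD endpoints at each evaluation time point after treatment in each group". The list for visit V2 (Section 4.1.2.1) only refers PD sampling back to Table 2.

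**The concern.** Every value of the secondary PD endpoint is a difference from, or a ratio to, this one sample. If some subjects are sampled before a large steroid dose and others after it, the baseline does not mean the same thing across subjects. If most are sampled after it, the comparison with 168 h and later also crosses from an acute-steroid condition to one days removed from it. Any acute steroid effect on circulating cells or interferon-gene expression would then be mixed into the apparent effect of CM313.

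The exposure is not small by the protocol's own figures. Section 3.8.8.2 sets 0.5 mg/kg prednisone against 0.4 mg/kg methylprednisolone, a ratio of 1.25. So 100 mg methylprednisolone corresponds to 125 mg prednisone, about twice the 60 mg/day background maximum in Section 3.8.8.1 (125/60 = 2.08).

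With 8 CM313 subjects per dose level, a baseline that varies in this way is hard to see through. PD is also one of the inputs that Section 3.1 names for deciding on added dose levels. A baseline drawn on the wrong side of the steroid cannot be recovered later.

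**Working it through.** **Inputs.** Time is in hours relative to the start of the first infusion.

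- Steroid time s: between -3 and -1 (synopsis; Section 3.8.2.3).
- Baseline sample time t: between -2 and 0 (Table 2).
- Group sizes: 8 CM313 and 2 placebo per dose level (Section 8.1).
- The protocol states no figure for this point, so there is none to reproduce.

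**Step 1. Order allowed by the windows.** Share of the permitted sampling window that lies after the steroid = (0 - max(s, -2)) / 2.

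| Steroid given at | Share after steroid |
|---|---|
| -3, -2.5 or -2 h | 2/2 = 100% |
| -1.5 h | 1.5/2 = 75% |
| -1 h | 1/2 = 50% |

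A baseline before the steroid needs both times to fall between -2 and -1 h, with the sample first.

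**Step 2. How often, under an assumption.** Take s and t as independent and uniform in their windows. P(sample first) = 1/2 × 1/2 × 1/2 = 1/8. So 7/8 = 87.5% of baselines follow the steroid. A simulation of 2,000,000 draws gives 87.5%, with a median gap of about 1.1 h; the windows allow at most 3 h.

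**Step 3. Mixed baselines in one group.** If each subject independently has chance p of a post-steroid baseline, P(both kinds present among n) = 1 - p^n - (1-p)^n.

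| p | n = 8 | n = 10 |
|---|---|---|
| 0.50 | 99% | 99.8% |
| 0.70 | 94% | 97% |
| 0.875 | 66% | 74% |
| 0.95 | 34% | 40% |

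If each site keeps a fixed routine, subjects are not independent and the mixture lies between sites instead. Site practice is not known.

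**Step 4. What the baseline is compared with.** If the infusion ends at midday, the last post-infusion steroid can fall late on the second following day, about 60 h later. The 168 h sample may be drawn at 168 - 24 = 144 h. The gap is then 144 - 60 = 84 h, or 3.5 days. For 336 h it is (336 - 24) - 60 = 252 h (10.5 days), and for 504 h it is (504 - 72) - 60 = 372 h (15.5 days). The 24 h sample falls around the first post-infusion steroid dose, so it is not a clean comparison under any baseline.

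**Step 5. Illustration of size only.** Suppose the steroid lowers an absolute count by a fraction f at the baseline draw, and CM313 truly lowers it by d at 168 h. Reported change = (1-d)/(1-f) - 1.

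| True change | f = 0 | f = 10% | f = 30% | f = 50% |
|---|---|---|---|---|
| -50% | -50% | -44% | -29% | 0% |
| -30% | -30% | -22% | 0% | +40% |

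The values of f are assumed. The protocol gives neither size nor direction for the steroid effect, and the formula need not hold if a subset is reported as a proportion.

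**The case against.** **The order may be fixed elsewhere.** Section 5.5.2 says "A separate Sample Management Manual will specify the sampling, storage, and transportation procedures to be followed for this study", and that manual is not shown. This stands in part. A manual could ask for the sample before the steroid, but both protocol windows can then be met only when the steroid is given less than 2 hours before infusion. With the steroid at 2 to 3 hours, a sample drawn first breaches Table 2. A manual could instead place every sample after the steroid. That would remove the mixing but keep the post-steroid baseline. The protocol does settle such an order in another case: Section 5.2.3 places the ECG before blood collection or at least 20 minutes after it.

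**Placebo subjects receive the same premedication.** True, and under blinding the order should not differ systematically by arm. The protection is partial: there are 2 placebo subjects per dose level, and the planned analysis is descriptive within group.

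**The consequence is limited.** Also true. No test is powered on this endpoint, and escalation between the planned levels rests on safety.

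**Stronger readings that the protocol does not support.** A reader might infer that CM313 depletion will be understated by a known amount; no steroid effect is given, so no amount follows. A reader might take the later samples as free of steroid; background corticosteroids continue as standard of care, so those samples are clear only of the infusion-related steroid. A reader might treat the pre-dose samples at dose 2 and the last dose as faulty baselines too; they are follow-up values. When a dose 2 sample and the baseline both follow the 100 mg dose, the comparison is like with like.

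**Conclusion.** The point holds as a fault of sampling order. The two windows make a post-steroid baseline certain when premedication is given 2 to 3 hours before infusion, and leave the order open when it is given 1 to 2 hours before. This affects the only baseline of a secondary endpoint and of the exploratory interferon-gene endpoint.

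The overlap follows directly from the text and needs no assumption. The 87.5% and 66% figures rest on uniform, independent timing; over per-subject chances of 50% to 95%, the second ranges from 99% to 34% for 8 subjects. The size and direction of any bias remain unknown, and Step 5 shows only how sensitive a ratio to baseline would be. The change should be made, because an uncontrolled baseline cannot be repaired afterwards. The primary safety objective does not depend on it.

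**What to change.** In Table 2, require the first-dose immune-cell and interferon-gene baseline samples to be drawn before the pre-infusion corticosteroid. Extend that sampling window earlier than 2 hours so that it stays feasible across the whole premedication window. Record the clock times of the sample and of the steroid. Apply the same order to the pre-dose PD samples at dose 2 and the last dose, so that they are comparable with the baseline. Carry the wording into the Sample Management Manual.

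The premedication regimen stays as it is. Sections 3.8.2.3 and 3.8.8 should be reconciled on whether premedication is recommended or required, since the difference can add variation between subjects.

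The cost is a line in Table 2 and in the manual, with no added visit or sample volume. There are two downsides. The PD tube may have to be drawn separately from the pre-dose PK tube. The 24 h change will then carry both steroid and CM313 effects, so it should be read against placebo at the same time point, pooled across dose levels (4 × 2 = 8 subjects, or 3 × 2 = 6 if the optional 16 mg/kg level is not opened).
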